## Abstract

**Background/Objectives:** Weight gain is frequently observed during and following breast cancer therapy. Women with overweight/obesity have poorer breast cancer prognoses and are more likely to develop comorbidities. The present study describes the development and qualitative assessment of the acceptability of the NutriLife study, a lifestyle weight management intervention with dietetic counseling and digital tools for breast cancer survivors (BCSs). **Methods:** The intervention was developed using the Medical Research Council (MRC) framework, informed by a systematic literature review and stakeholder input. Acceptability was assessed using the Theoretical Framework of Acceptability (TFA). A total of 22 BCSs with overweight/obesity participated in focus groups, and 5 dietitians/nutritionists specializing in breast cancer in Greece participated in semi-structured interviews. The data were further analyzed using thematic analysis. **Results:** Stakeholders assessed the intervention as acceptable across all TFA constructs. The intervention was characterized as supportive, easily adaptable, time-efficient, well-organized, beneficial, and professionally driven, with potential barriers including limited personal time, inadequate digital literacy, insufficient self-care, and lack of commitment. Gradually increasing goals may be helpful and less stressful, while educational resources enhance focus on these objectives, thus encouraging intervention participation. Ensuring confidentiality was perceived as central to promoting health. **Conclusions:** The evidence-based, co-participatory design of the NutriLife intervention was perceived as acceptable by the participating stakeholders and will be pilot-tested in a randomized controlled trial.

## 1. Introduction

A growing body of evidence confirms that obesity is a recognized risk factor for the initiation, progression, and metastasis of breast cancer [1,2,3]. Obesity appears to increase the risk of breast cancer and its recurrence by raising oestrogen levels, promoting inflammation, and contributing to the development of metabolic syndrome [4]. A meta-analysis of 82 studies including over 200,000 patients revealed that the mortality risk increased by 75% in premenopausal women and by 34% in postmenopausal women if they were living with obesity at the time of breast cancer diagnosis, compared to patients with normal body weight [5]. Breast cancer survivors often gain weight, which is linked to a higher risk of comorbid conditions such as type 2 diabetes and cardiovascular disease [6]. A meta-analysis encompassing 12 studies with a total of 23,832 women showed that women who increased their initial body weight by at least 5% after their post-breast cancer diagnosis were at increased risk of mortality from all causes compared to women whose body weight remained stable (HR, 1.12; 95% CI, 1.03–1.22). In fact, mortality risk was highest among patients who experienced a body weight increase of at least 10% [7].

Although the association between intentional weight loss and survival outcomes following primary breast cancer treatment remains unclear, weight loss may reduce the risk of comorbidities. Several leading health authorities recommend managing excess weight in individuals living with or surviving cancer [1,8]. Strategies for managing body weight include preventing weight gain, pursuing intentional weight loss, and maintaining weight loss, emphasizing the importance of counseling to provide ongoing support for behavioral changes among survivors [9,10]. Recent studies indicate that effective weight gain prevention or weight loss interventions must integrate structured physical activity and dietary modifications and should be based on evidence-based behavior change theories and techniques [11,12,13]. These interventions should tackle perceived barriers to weight loss, such as symptoms from breast cancer treatment and fatigue, thereby addressing the unique needs of this population [14].

In order to minimize the impact of obesity on breast cancer, interventions must be complex yet pragmatic in design [11], ensuring that they are acceptable and equally accessible to all women [15]. An intervention may also incorporate existing evidence and/or experience. The study design of such interventions needs to be tailored according to the research questions and the selected outcome measures [16]. It is recommended to integrate appropriate theories or theoretical models and frameworks at the study design stage, drawing on existing evidence and theoretical frameworks from relevant disciplines while engaging different stakeholders. This concept should be refined throughout the research process to yield an updated program theory upon project completion [16]. The Medical Research Council (MRC) and the National Institute for Health Research proposed a new framework that considers recent developments in theory and methods, aiming to enhance the efficiency, utilization, and impact of research [16]. This framework seeks evidence that the key components are addressed in the research design and implementation.

‘Intervention acceptability’, that is, the acceptance of the intervention by both intervention deliverers (e.g., dietitians/nutritionists) and recipients (e.g., breast cancer survivors) constitutes an essential prerequisite for successful intervention implementation [17]. Therefore, intervention acceptability should be considered in the design of healthcare interventions, particularly in contexts characterized by complexity and multiple interacting components [18].

The present study represents the formative phase of the NutriLife intervention and aligns with the updated Medical Research Council (MRC) framework for developing and evaluating complex interventions. While prior studies have addressed weight management in breast cancer survivors, few have integrated theory-based frameworks (MRC, TFA), stakeholder co-creation, and hybrid delivery formats (in-person, group, and digital) within a culturally specific Mediterranean context. This manuscript focuses on the development process and, critically, the qualitative evaluation of the intervention’s acceptability among key stakeholders—namely, breast cancer survivors and oncology-specialized dietitians/nutritionists. A randomized controlled trial has been registered (NCT06577545) and will assess the feasibility, adherence, and preliminary effectiveness of the intervention in the next research phase. The primary aim of the current study is to assess the perceived acceptability of the NutriLife intervention using qualitative methods, in accordance with the Theoretical Framework of Acceptability (TFA). By capturing end-user perspectives, this study aims to inform future adaptations and support the intervention’s implementation readiness.

## 2. Methods

### 2.1. Development of the NutriLife Intervention

The NutriLife intervention is a lifestyle weight management intervention with dietetic counseling and digital tools for breast cancer survivors living with overweight/obesity. It was guided by the Medical Research Council (MRC) framework for the development and evaluation of complex interventions [16], designed by a multidisciplinary group of researchers (dietitians/nutritionists, oncologists, physical education instructors, and clinical and health psychologists) and co-created by stakeholders (breast cancer survivors and dietitians/nutritionists). The MRC framework divides complex intervention research into four phases: development or identification of the intervention, feasibility, evaluation, and implementation. Accordingly, the design of the NutriLife intervention was developed based on a systematic review and by using a co-participatory approach with breast cancer survivors and dieticians/nutritionists specializing in cancer care. The systematic review was conducted to identify the effective behavioral change techniques in nutrition and physical activity interventions for treating overweight or obesity in post-treatment breast cancer survivors [19]. The behavioral change techniques found to be the most effective were the main constructs of the intervention’s context. Furthermore, a qualitative study (focus groups) was conducted to examine the barriers and facilitators influencing breast cancer survivors’ adoption of a healthy lifestyle, as well as to gather their recommendations for the development of weight management interventions [20]. Interviews with dietitians/nutritionists specializing in cancer care were held to evaluate their views and perspectives influencing lifestyle and weight management in breast cancer survivors [21]. The findings of these three preparatory studies were combined to develop an evidence-based intervention for treating overweight/obesity in breast cancer survivors. The co-participatory approach used in its design is expected to increase its potential effectiveness. Prior to the implementation of the NutriLife intervention, the feasibility of the intervention’s design and the evaluation of the intervention’s content were assessed through an acceptability study, as described below.

#### 2.1.1. The NutriLife Intervention: Duration, Content, Target Population, and Deliverers

Breast cancer survivors are defined as women who have received a diagnosis of breast cancer and have completed overall treatment, including surgery, chemotherapy, radiotherapy, and other cancer treatments, excluding hormone or immune therapy.

The study participants in both arms will consist of female breast cancer survivors at least 3 months post-treatment (including surgery, chemotherapy, radiotherapy, or other cancer treatments) and without active cancer therapy or ongoing treatment, except for hormonal or immune therapy. The participants will be aged 18–65 years, have a BMI of 25–40 kg/m^2^, and will not adhere to a specific diet plan during the study period. Everybody must have access to a computer or smartphone, internet connectivity, and the ability to operate a computer. Exclusion criteria will include breast cancer survivors with active cancer, morbid obesity (BMI > 40 kg/m^2^), those on weight-loss medication, pregnant individuals, or those with any medical condition that would preclude participation in a diet and exercise program.

The duration of the NutriLife intervention will be 24 weeks, combining individual, group, and digital sessions (with the use of asynchronous methods) grounded in the principles of Bandura’s Social Cognitive Theory (SCT) [22]. Therefore, the content of the weight loss intervention will be based on the identified theoretical constructs and the behavioral change techniques (BCTs) that were identified by the systematic review. The sessions will mainly focus on the determinants that have been recorded through the two qualitative studies (focus groups with breast cancer survivors and interviews with health professionals). Those determinants are categorized into three main factors—individual, social, and environmental—which inform the intervention’s contents, enhanced by BCTs such as social support, education, personalized diet plan, advice and goals, flexible recommendations, and a follow-up plan.

Both individual and group sessions will be led by registered dietitians/nutritionists (RDNs). Group sessions will involve both RDNs and clinical psychologists. A team consisting of RDNs, oncologists, clinical psychologists, and physical activity (PA) coaches will facilitate the digital sessions.

Over the 6-month intervention period, the participants will receive 5 individual counseling sessions, 4 group sessions, and 15 digital sessions. The contents of the intervention are available in Supplemental Material S1.

#### 2.1.2. Intervention Targets and Outcomes

The primary outcome of the 6-month intervention is to achieve and maintain a 10% reduction in initial body weight. To achieve the targeted weight loss, the participants will receive a personalized diet plan aimed at reducing energy intake, creating an energy deficit of 500 to 1000 kcal per day, based on their initial body weight and energy requirements. The diet plan will be formulated according to Mediterranean diet guidelines, emphasizing a plant-based approach that is rich in fruits, vegetables, and fiber, while restricting sugar, alcohol, and processed meats/foods. Individualized guidance will be provided to facilitate the achievement of dietary goals.

In relation to the target of physical activity, it is advised that each exercise session exceed 30 min, preferably conducted daily, with a gradual increase in duration over time. The participants will be encouraged to engage in either organized workout sessions or increase their regular physical activity, such as walking or swimming. The participants will be provided with a pedometer to monitor their daily steps. The number of steps and the minutes spent participating in physical activity will be compared to the weekly target.

The participants will be encouraged to submit their weight loss, dietary, and physical activity records on a weekly basis to self-monitor their weight status and lifestyle modification progress.

Furthermore, individuals will receive written materials in line with the World Cancer Research Fund (WCRF) recommendations regarding nutrition and physical activity for breast cancer survivors [1].

#### 2.1.3. Plan for Quantitative Assessment of NutriLife Intervention Effectiveness

The impact and outcome evaluation of the NutriLife intervention will be tested through a randomized controlled trial (RCT), using an intervention and a control group.

The NutriLife intervention will be implemented and evaluated according to the timeline presented in Figure 1.

#### 2.1.4. Sample Size and Randomization

The sample size calculation foreseen for the RCT is presented in Supplemental Material S2. Briefly, after assuming that in the intervention-guided arm of our study, 25% of the participants will lose at least 10% of their baseline body weight, while in the control group, 4% of the participants will lose at least 10% of their baseline body weight, as well as after assuming a 10% drop-out rate during the 6-month period, a sample size of 92 participants (46 participants in each arm) is deemed sufficient to detect a statistically significant difference at a 95% confidence level with 80% power [23].

Women will be randomly assigned to one of two study groups using a random permuted block design. To ensure the homogeneity of the groups, the research group will consider multiple factors such as age, menstruation, education level, financial status, employment status, marital status, and place of residence. Research staff responsible for assessing forms and inputting data will be unaware of the participants’ assigned study group, thereby ensuring blinding. Subsequent to randomization, a member of the research team will contact each participant to inform them as to which group they were assigned and to arrange the first meeting.

#### 2.1.5. Measurements and Procedures

Measurements will be conducted in laboratories and clinics during the intervention phase at weeks 1, 12, and 24 and at the end of the follow-up phase at week 48. During the baseline visit (week 1), measures of body weight, height, waist, and hip, in conjunction with a body composition analysis and all questionnaires, will be collected. In the middle of the intervention at week 12, only body weight and a satisfaction survey will be assessed. Body weight, waist and hip circumference, body composition analysis, and all baseline questionnaires will be evaluated at the final visit (week 24).

Initially, a questionnaire relating to the medical history of the participants will be administered, following another survey focusing on sociodemographic characteristics.

Considering dietary intake, a 24 h dietary recall and a 120-item food frequency questionnaire (FFQ) will be used. Adherence to the Mediterranean diet will be assessed using MedDietScore [24].

The assessment of physical activity levels will be conducted using the modified International Physical Activity Questionnaire (IPAQ).

The SF-12 questionnaire will be used for the evaluation of mental and physical health, as both factors significantly influence an individual’s overall quality of life. Additionally, the Impact of Weight on Quality of Life–Lite (IWQoL-Lite) questionnaire will be utilized to evaluate the quality of life experienced by breast cancer survivors.

The assessment of sleep will be conducted using the Pittsburgh Sleep Quality Index.

The Body Image and Relationships Scale (BIRS) and the 4-item Concerns about Recurrence Questionnaire (CARQ-4) will be measured.

Psychological outcomes, particularly self-efficacy as measured by the Rosenberg scale, depression as assessed by the CES-D (Patient Health Questionnaire-8), and anxiety as evaluated by the 20-item state-trait anxiety index, will also be included in the assessment.

In the context of the study, the attendance rates of individuals participating in in-person and group sessions, the frequency of weekly weight, diet, and exercise log submissions, the level of adherence to diet and activity goals on a weekly basis, and the extent to which the participants comply with follow-up sessions will be examined. Moreover, the participants’ (breast cancer survivors’) level of adherence to the intervention, perceived barriers and facilitators for its implementation and satisfaction, as well as all intervention costs will be recorded through questionnaires.

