## 5. Strengths and Limitations

The NutriLife intervention was developed through a multidisciplinary, theory-driven, and co-creative approach that aligns with current best practices in complex intervention design. Its integration of the Medical Research Council (MRC) framework and the Theoretical Framework of Acceptability (TFA), in combination with Social Cognitive Theory (SCT), enhances both conceptual rigor and practical relevance.

Specifically, the NutriLife intervention incorporates

(a)a multidisciplinary team of healthcare professionals (dietitians/nutritionists, oncologists, physical activity experts, and psychologists) for its development;(b)personalized in-person nutritional counseling aimed at enhancing self-efficacy;(c)group-mediated cognitive behavioral support and peer interaction to foster self-regulation and problem-solving skills;(d)individualized dietary guidance tailored to patients’ specific needs; and(e)evidence-based, asynchronous digital tools that support behavioral weight management and promote maintenance of newly acquired behaviors.

Despite these strengths, several limitations must be acknowledged. Recruitment via online platforms likely introduced self-selection bias, favoring participants already motivated toward lifestyle change. The participants were predominantly well-educated and digitally literate, which may limit generalizability to underserved or digitally excluded populations. The remote nature of qualitative data collection may have limited the observation of nonverbal cues. The use of self-reported anthropometric data introduces recall and social desirability bias. Although standard procedures were applied, researcher bias may have influenced the data interpretation. Lastly, the intervention was developed and tested qualitatively within a specific regional and cultural context in Greece; thus, its applicability to other cultural or healthcare systems should be approached with caution until further testing is conducted.

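### Section 2.1.5 misidentifies two psychological measures: self-efficacy is tied to a self-esteem scale, and the depression instrument carries the names of two different questionnaires

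*Protocol article*

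**What the plan says.** Section 2.1.5 (Measurements and Procedures) of the protocol article assigns one instrument to each of three psychological outcomes, all in one sentence:

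- Self-efficacy and depression: "self-efficacy as measured by the Rosenberg scale, depression as assessed by the CES-D (Patient Health Questionnaire-8", where the last name stands in parentheses as if it explained the one before it.
- Anxiety: "anxiety as evaluated by the 20-item state-trait anxiety index".

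The same section has the baseline questionnaires completed at week 1 and again at week 24. Week 12 is limited to body weight and a satisfaction survey.

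Self-efficacy also appears where the article describes the intervention. Section 2.1.1 grounds the sessions in Social Cognitive Theory, and section 5 (Strengths and Limitations) lists "personalized in-person nutritional counseling aimed at enhancing self-efficacy" among the features of the programme.

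**The concern.** A trial can report on a construct only if the instrument measures it. If the sentence is followed literally, a Rosenberg score will be published as self-efficacy. A change in that score, or the lack of one, would then be read as evidence on whether counselling raised women's confidence in changing their diet and activity. A self-esteem score cannot answer that question.

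For depression the problem is identification. With two instrument names for one outcome, a reader cannot tell which items are asked, how they are scored, or which score will be compared between arms. Until this is settled, the form could be prepared inconsistently, or the score chosen after data are in hand. The text shows neither happening, but it does not rule them out.

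**Working it through.** No arithmetic applies. The check sets the relevant places in the article side by side.

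**Step 1: what the article means by self-efficacy.** Table 1, written for the qualitative acceptability study, describes self-efficacy as a participant's confidence that she can carry out what the programme asks of her. Section 3 uses the word the same way when it reports that many survivors doubted they could keep to the objectives or handle the technology. Section 4 responds by calling for strategies to build confidence. In this article, then, self-efficacy is confidence about specific behaviours.

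**Step 2: what the Rosenberg scale measures.** The article gives no fuller name, item content or citation for it. By its standard name it is a self-esteem scale, that is, a measure of general self-worth. This step rests on common knowledge of a standard instrument, not on the article's text. If it is granted, the instrument does not measure the construct described in step 1.

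**Step 3: whether another listed measure fills the gap.** The remaining instruments in section 2.1.5 cover:

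- medical history and sociodemographic characteristics;
- diet (24-hour recall, food frequency questionnaire, MedDietScore);
- physical activity (modified IPAQ);
- general mental and physical health (SF-12);
- weight-related quality of life (IWQoL-Lite);
- sleep (Pittsburgh index);
- body image (BIRS) and concern about recurrence (CARQ-4);
- anxiety.

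The process measures cover attendance, log submission, adherence to goals, costs and "perceived barriers and facilitators for its implementation and satisfaction". These record behaviour and experience. None is a self-efficacy scale.

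**Step 4: the depression instrument.** CES-D is not an abbreviation of Patient Health Questionnaire-8. They are two separate questionnaires with different items and scoring. No other place in the article says which is meant. The SF-12 covers mental health in general and does not supply the missing depression score.

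**Step 5: what depends on these measures.** Section 2.1.2 defines the primary outcome as a 10% reduction in initial body weight. Section 2.1.4 derives 92 participants (46 per arm) from assumed proportions of 25% and 4% losing at least 10% of baseline weight, with 10% drop-out and 80% power. No psychological score enters either section.

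**Result.** Two of the three outcomes in the sentence are misidentified. Neither is corrected elsewhere in the article, and neither touches the primary analysis.

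**The case against.** The strongest reply is that this may be no more than careless wording. The article does not spell out the Rosenberg scale, so the text cannot show whether the trial picked an unsuitable instrument or merely used the wrong word for a suitable one. If only the word is wrong, the measurement is sound and a new label settles it. That is a fair point, and it is why relabelling is offered as a full remedy. It does not remove the finding, because one of the two, label or instrument, has to change. Nor does the shortness of a journal article excuse it: the article chose to name the instruments, and the names do not fit.

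Three stronger readings are tempting, and the article does not support them.

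- A reader might infer that the trial fails to measure the core mechanism of the intervention. No section calls self-efficacy the core mechanism or announces a mediation analysis. It is one target among several. Section 2.1.1 describes content "enhanced by BCTs such as social support, education, personalized diet plan, advice and goals, flexible recommendations, and a follow-up plan", and section 5 also names self-regulation and problem-solving. Depression is not presented as a mechanism at all.
- A reader might infer that two depression questionnaires will be given together. A parenthesis that mislabels one form is the simpler explanation. The defect is an unidentified instrument, not proven double measurement.
- A reader might infer that forms could differ between baseline and follow-up by design. Section 2.1.5 already has the baseline questionnaires repeated at week 24, so no such defect is shown.

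It can also be said that counting two of three looks only at one sentence, since the SF-12, BIRS and CARQ-4 have psychological content too. That is correct, and the count should be read only in that sense.

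**Conclusion.** The point holds as a misidentification of two non-primary psychological measures. Self-efficacy has no matching instrument in the trial as described, and the depression score is not identified. The depression half needs only the recognition that the two names belong to different questionnaires. The self-efficacy half assumes that the Rosenberg scale is the self-esteem scale commonly known by that name. How much is lost depends on a fact the article does not give, namely which forms are actually in use. If the forms are right and the wording wrong, only the text needs correcting. If the Rosenberg form is meant to answer the self-efficacy question, that question goes unanswered. The finding merits correction before the trial collects data, but it does not threaten the trial's main result.

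**What to change.** Make two changes before baseline data collection. Section 6 still describes the trial as forthcoming.

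1. **Self-efficacy.** Either relabel the Rosenberg outcome as self-esteem and make no self-efficacy claim from it, or replace it with a validated self-efficacy scale, for example one for diet, exercise or weight control. If the sponsor wants to report whether counselling improved self-efficacy, only the second option serves.
2. **Depression.** Name one instrument, either the CES-D or the PHQ-8, and delete the other name.

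If the forms in use are already the intended ones, the cost is a wording correction. Otherwise it is a questionnaire swap with similar respondent burden and no added visit. The sample size, the visit schedule and the primary analysis stay as they are.
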